### Primary outcomes

The first primary outcome will be adherence to a complete AL course (doses 2-6) measured in category 3 only and defined as: a) adherent, if they present with empty blister packs and report taking the medications as recommended (± 1 hour for dose 2 and ± 2 hours for doses 3-6); b) probably adherent if they do not present blister packs but report taking the medications as recommended, c) probably non adherent if they do not present blister packs and do not report taking the medications as recommended, and d) non adherent if they present blister packs with at least one tablet not used. The second primary outcome will be the proportion of patients reporting to the health facility for the day 3 post treatment review for the evaluation of clinical and parasitological cure at day 3 (only category 1 and 2).

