Poor patient adherence to treatment and drug misuse are among some of the drivers of resistance [11]. Poor adherence is likely to decrease cure rates and to favour the emergence of resistance because parasites are exposed to sub therapeutic drug concentrations. Evidence from systematic reviews suggests variable outcomes of adherence to malaria treatment, ranging from sub-optimal (less than 50%) to very high (90-100%) [12–15]. The varying adherence estimates are probably due to factors related to patient characteristics and the nature of their consultation with the provider or methodological variations such as the interaction between the research team and patients before and during treatment. A recent systematic review has suggested that future studies of adherence to malaria treatment could benefit from an awareness of the impact of study procedures on adherence outcomes, and has proposed the identification of improved measurement methods less dependent on self-reporting [13]. Presently, the most widely used methods for adherence measurement are conducted after completion of a full dose of Artemether-Lumefanthrine (AL). However, these methods rarely consider the timing of dosing and depend on self-reporting which has inherent recall bias resulting in unreliable measurements of adherence to AL dosing schedules. AL is presently the most widely used artemisinin combination therapy (ACT) in rural Africa, but AL has a relatively complex dosing scheme, requiring twice a day drug administration with the second dose spaced 8 hours after the first dose. From literature review, only one study has attempted to measure the timing of individual AL doses [16]. There is therefore a need to investigate better approaches for measuring and improving adherence to malaria treatment and this research aims to provide the much needed evidence base.

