### Phase 2 – The randomized controlled trial

**Trial design:** Caregivers of eligible children with uncomplicated malaria will be randomly assigned (one to one) to two different arms: 1) the current standard of care based on provider counselling and health education alone, and 2) the current standard of care plus SMS reminders. Within each arm participants will be further randomly assigned to 3 different categories for the measurement of adherence to the different doses of AL. In the first category, 600 caregivers (300 per arm) will be visited at home on day 1 of follow up to measure adherence and timing of the second AL dose; in the second category, another 600 caregivers (300 per arm) will be visited at home on day 2 to measure adherence and timing of AL doses, 3 and 4, while, in the third category, a final 800 caregivers (400 per arm) will be reviewed at home on day 3 after they have completed the full treatment course to measure adherence for the full course of AL. All caregivers in each category will be visited at home only once to avoid biases in the subsequent measures of adherence as a result of the consultations at home. Caregivers in category 1 and 2 will be required to come to the health facility for the day 3 post treatment reviews, while those in category 3 will be visited at home on day 3.

AL will be administered according to weight bands: 5-14 kg, 1 tablet twice a day for three days, 15-24 kg, 2 tablets twice a day for three days and will be directly observed for the first dose, with the remaining 5 doses being provided for administration at home. All caregivers will receive standard instructions about how to administer AL at home and when to return to the facility for scheduled visits or immediately if unwell. At first dose administration, the telephone numbers of all eligible caregivers will be registered into the automated system by the randomizing nurse who will also observe directly supervised therapy of the first dose. The registration will record the time when the first dose is administered. A procedure for guiding the correct registration of the random number that will act as a unique identifier has been put in place (Figure 2).

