### Quality control and limitation of bias

The major source of bias in adherence studies is reliance on participant recall and the possibility of false reporting. We have adopted an innovative approach of measuring adherence on different days during the dosing period, which is likely to reduce recall bias for the doses on days 1 and 2 in category 1 and 2 but not in category 3. The second primary outcome measure (day 3 post treatment review) requires objective assessment and we do not anticipate any biases in its measurement. The trial will be conducted under strict adherence to good clinical practice (GCP) standards.

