### Measurement of the efficacy of the SMS intervention on adherence

At each of the time points (day 1, 2 and 3); caregiver reports and pill counts will be used for measuring adherence in the intervention and control arms. While the day 1 and day 2 visits could result into slightly better adherence for doses, 3 and 4 because they are visited at home in the early days of follow up, category 3 will provide closer to real life adherence as these patients will only be visited at home after completion of the treatment course.

Measurement of the efficacy of the SMS intervention on day 3 post treatment reviews

At enrolment, all caregivers will be informed about the importance of a day 3 post treatment review from a clinical and drug resistance surveillance perspective, to confirm a malaria free status at day, or anytime during follow up if unwell for a period of 28 days. The proportion returning for the day 3 post treatment reviews will be determined in the intervention and control arms.

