**Figure 2 F2:**
[figure not shown]
Algoritham.

**Table 1 T1:** Timing and content of messages.

Confirmation message (at the time of dose 1 on Day 0)	Hello (CAREGIVER NAME), this message is to confirm that you are now registered into the SMS malaria study. Thank you (HF Name)
Dose 2 reminder (8 hours after dose1 on Day 0)	Hello (CAREGIVER NAME), have you remembered to give your child dose 2 of malaria medicine? If not, please do so. Thank you, (HF Name)
Dose 3 reminder (8.00 am on Day 1)	Hello (CAREGIVER NAME), have you remembered to give your child dose 3 of malaria medicine? If not, please do so. Thank you, (HF Name)
Dose 4 reminder (8.00 pm on Day 1)	Hello (CAREGIVER NAME), have you remembered to give your child dose 4 of malaria medicine? If not, please do so. Thank you, (HF Name)
Dose 5 reminder (8.00 am on Day 2)	Hello (CAREGIVER NAME), have you remembered to give your child dose 5 of malaria medicine? If not, please do so. Thank you, (HF Name)
Dose 6 reminder (8.00 pm on Day 2)	Hello (CAREGIVER NAME), have you remembered to give your child dose 6 of malaria medicine? If not, please do so. Thank you, (HF Name)
Day 3 review reminder^*^ (8.30 pm on Day 2)	Hello (CAREGIVER NAME), please remember to bring the child back to hospital tomorrow to confirm clearance of malaria parasites. Thank you, (HF Name)
Day 3 review reminder^*^ (8.00 am on Day 3)	Hello (CAREGIVER NAME), please remember to bring child back to hospital today to confirm clearance of malaria parasites. Thank you, (HF Name)
Day 7 unscheduled visit reminder (8.00 am on Day 7)	Hello (CAREGIVER NAME), I hope the child is doing well. If not, please bring them back to the hospital as soon as possible. Thank you, (HF Name)
Day 14 unscheduled visit reminder (8.00 am on Day 14)	Hello (CAREGIVER NAME), I hope the child is doing well. If not, please bring them back to the hospital as soon as possible. Thank you, (HF Name)
Day 21 unscheduled visit reminder (8.00 am on Day 21)	Hello (CAREGIVER NAME), I hope the child is doing well. If not, please bring them back to the hospital as soon as possible. Thank you, (HF Name)
Day 28 review reminder (6.00 pm on Day 27)	Hello (CAREGIVER NAME), Please bring your child back to the hospital tomorrow for day 28 review as advised by the doctor. Thank you, (HF Name)
Day 28 review reminder (8.00 am on Day 28)	Hello (CAREGIVER NAME), Please bring your child back to the hospital today for day 28 review as advised by the doctor. Thank you, (HF Name)

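### The first primary outcome depends on dose times reported on day 3 to within 1-2 hours, and the SMS may cue those reports in one arm only, so reporting error could differ by arm and mimic an adherence effect

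*Protocol article*

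**What the plan says.** The first primary outcome is "adherence to a complete AL course (doses 2-6) measured in category 3 only" (Primary outcomes). The adherent class needs empty blister packs and a caregiver who can "report taking the medications as recommended (± 1 hour for dose 2 and ± 2 hours for doses 3-6". A second class needs no pack at all: "probably adherent if they do not present blister packs but report taking the medications as recommended". Category 3 caregivers "will be reviewed at home on day 3 after they have completed the full treatment course to measure adherence for the full course of AL" (Phase 2, Trial design). The instruments are stated under Measurement of the efficacy of the SMS intervention on adherence: "caregiver reports and pill counts will be used for measuring adherence in the intervention and control arms".

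The same section on trial design sends dose reminders to the intervention arm only: eight hours after dose 1 for dose 2, then at 8 am and 8 pm until the course ends. Table 1 shows a separate message for each dose, for example "have you remembered to give your child dose 2 of malaria medicine".

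On measurement error, the Background says that the usual post-treatment methods "depend on self-reporting which has inherent recall bias resulting in unreliable measurements of adherence to AL dosing schedules". Quality control and limitation of bias says that the staggered visits are "likely to reduce recall bias for the doses on days 1 and 2 in category 1 and 2 but not in category 3".

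**The concern.** Recall error of the same kind in both arms would mainly lower and blur both adherence estimates. Here the intervention itself may act on the measuring instrument. A caregiver who received a message naming dose 4 at 8 pm has a cue for when dose 4 was due, and may report that time whether or not the dose was given then. The cue exists in one arm only and would remain if the home visitors were fully masked.

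The article treats recall bias in category 3 as a general limitation. Its reassurance about unmasked home visitors, that the visit follows the dose, means that the visit cannot change dosing. It does not address how dose times are reported.

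At stake is the reading of a positive result on the first primary outcome. The cost-effectiveness ratio per additional adherent child would carry the same error.

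**Working it through.** **Inputs from the article.** Control adherence 65%, 10-point target, 400 per arm, 15% loss, 80% power, 5% level (Sample size estimation). Two-sided testing is assumed. Missing adherence counts as failure among all randomised (Trial Data Analysis).

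**Inputs assumed.** All error rates below; the article gives none. True adherence is 65% in both arms, so every gap is spurious. An empty pack with reported times outside the windows fits none of the four stated classes; it is taken here as not adherent.

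**1. The plan's own figure.** n = [1.96·√(2p̄(1−p̄)) + 0.8416·√(p₁(1−p₁)+p₂(1−p₂))]²/d², with 0.65, 0.75 and p̄ = 0.70, gives 329 per arm. Then 329/0.85 gives 388, or 349/0.85 gives 411 with continuity correction. The stated 400 lies between and is reproduced. With 400 × 0.85 = 340 evaluable per arm, power is 81%.

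**2. Length of recall.** Recruitment stops by 2 pm and dose 2 is prompted 8 hours after dose 1, so dose 2 is due by about 10 pm on day 0. At a daytime visit on day 3 it is more than two days old.

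**3. Leverage of five doses.** If doses are independent and equally likely to be in window, 65% overall needs 0.65^(1/5) = 91.7% per dose and 75% needs 0.75^(1/5) = 94.4%. A shift of 2.7 points per dose produces the whole target effect.

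**4. Three error models.**
- A, on-time doses recalled as off-time: reported adherence = 0.65·q⁵, where q is the chance that an on-time dose is recalled in window.
- B, a share f of non-adherent SMS caregivers reports the message times: 0.65 v 0.65 + 0.35f.
- C, errors both ways: (0.917q + 0.083m)⁵, where m is the chance that an off-time dose is reported as on time. Better recall raises q and lowers m.

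Chance of a significant result favouring SMS (nominally 2.5%) = Φ{[d − 1.96·√(2p̄(1−p̄)/n)]/√[(p₁(1−p₁)+p₂(1−p₂))/n]}. Gaps are in percentage points, from unrounded values. The last column counts 15% missing as failures, so both rates are multiplied by 0.85 and n = 400.

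| Model, control v SMS | Reported % (340 per arm) | Gap; chance | Gap; chance (400, missing = failure) |
|---|---|---|---|
| A: q 0.95 v 0.98 | 50.3 v 58.8 | 8.5; 60% | 7.2; 53% |
| A: q 0.97 v 0.99 | 55.8 v 61.8 | 6.0; 35% | 5.1; 30% |
| A: q 0.97 v 0.98 | 55.8 v 58.8 | 2.9; 12% | 2.5; 10% |
| B: f = 0.20 | 65.0 v 72.0 | 7.0; 50% | 5.95; 40% |
| B: f = 0.10 | 65.0 v 68.5 | 3.5; 16% | 2.98; 13% |
| C: q 0.95 v 0.98, m 0.30 v 0.15 | 57.9 v 62.9 | 5.05; 27% | 4.3; 23% |
| C: q 0.95 v 0.98, m 0.50 v 0.25 | 63.4 v 65.8 | 2.4; 10% | 2.1; 8% |

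**5. The sign is not fixed.** In model C with m 0.80 v 0.40, the per-dose rates are 0.917 × 0.95 + 0.083 × 0.80 = 0.938 and 0.917 × 0.98 + 0.083 × 0.40 = 0.932. Over five doses this is 72.5% v 70.4%, a gap of 2.1 points against SMS. Better recall also removes false on-time reports.

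**The case against.** The strongest case against has five parts.

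- **The cue is inferred.** A reader might infer that each SMS leaves a time-stamped record that caregivers consult at the visit. The article does not say that messages are kept, show a time or are looked at, and the texts in Table 1 contain no clock time. Phones may be shared, and in the feasibility survey 73.8% of caregivers had a personal phone. This stands: the message may cue the report, and no more can be said.
- **Controls are not without a cue.** All caregivers receive standard instructions on giving AL at home, and controls can report that schedule back. This also stands. What remains is that controls get no message at each due time.
- **Better recall can work both ways.** Steps 4 and 5 confirm this. A model in which error only loses on-time doses overstates the gap.
- **The limitation is already acknowledged.** In part only: the article concedes recall error in category 3, but not that it may differ by arm. The per-dose outcomes in categories 1 and 2 shorten recall but are secondary and have the same imbalance in messages.
- **Sensitivity analyses are planned, and their detail belongs in the SAP.** True. A completion analysis may already be specified there, and its absence from the article is not the finding. The point concerns how the article fixes the outcome and what it says about bias.

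The empty-pack rule limits false reports of wholly missed doses in the adherent class. It does nothing for late doses, or for caregivers without a pack.

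**Conclusion.** The concern holds as a possibility that the plan should address. Timing in the first primary outcome rests on caregiver report alone, dose-specific messages go to one arm only, and the article does not consider that reporting error may differ by arm.

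The documents do not support the stronger reading, that the SMS will inflate reported adherence or by a known amount. Neither direction nor size can be derived from them. Under the assumed rates, the scenarios favouring SMS give spurious gaps of about 2 to 8 points against a 10-point target, and a more extreme choice reverses the sign. These figures show that modest differences per dose matter once five doses must all be in window. They do not estimate the bias in this trial.

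**What to change.** Keep the stated outcome and add the following.

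1. Pre-specify, beside the first primary outcome, a comparison by arm of course completion from the day-3 tablet count, ignoring reported clock times. In one version an unseen pack counts as not complete. In the other it is classified by whether the caregiver reports that all doses were given, so that caregivers without a pack are not all made failures.
2. Report its estimate and confidence interval beside the primary result. Agreement in sign alone is too weak a test: with no true effect on completion, the estimate would favour SMS about half the time by chance.
3. Describe an effect seen only in the timing component as an effect on reported timing, not as established better adherence.
4. State in Quality control and limitation of bias that recall error in category 3 may differ by arm because of the messages.

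The tablet count shows removal from the pack, not ingestion, and the second version still uses report for unseen packs; both limits should be stated. If the SAP already contains such an analysis, items 2 to 4 are enough. The cost is some wording, one extra analysis of data already collected, and a more guarded conclusion if the effect appears only in reported times.

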### Sample size estimation

The sample size estimation was based on the first primary outcome-adherence to the full course of AL treatment. Assuming a malaria treatment adherence of 65% with the current standard of care alone [30], a sample size of 400 participants in category 3 per arm will be able to detect a minimum desirable effect difference of 10% with 80% power at a 0.05 level of significance, assuming a 15% loss to follow up. In order to robustly measure adherence to the individual AL doses, we have included an additional 300 caregivers per arm in each of the first and second categories. This sample size will be sufficient to detect an effect difference of 10% around an estimated adherence of 75% to the individual AL doses, assuming a 10% loss to follow up. For the measurement of the day 3 post-treatment reviews, the combined sample size in categories 1 and 2 (600 per arm), has adequate power (over 90%) to detect a 10% effect difference around a conservative estimate of the proportion returning for day 3 post-treatment review of 45%. Therefore, we will recruit a total 1,000 caregivers for the study.

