### Laboratory procedures

At enrolment and at all scheduled visits at the health facility or at home (days 0, 3 and 28) and at all unscheduled visits, a blood smear will be taken for the estimation of parasite density. Screening thick blood smears will be stained with 10% locally prepared Giemsa for 10 minutes, while definitive thick and thin blood smears will be stained with 2% commercially prepared Giemsa for 30 minutes. The thick smears will be used to make the diagnosis of malaria, calculate parasite density and look for the presence of gametocytes, while the thin smears will be used for speciation. The number of asexual parasites per 200 WBCs will be counted, and if there are less than 10 parasites per 200 WBCs, the count will be continued until 500 WBCs. Parasite density will be estimated based on the assumption of a standard estimate of 8000 WBCs/UL. A blood smear will be deemed negative, if there are no asexual parasites after counting a hundred high power microscopic fields. In addition, haemoglobin level will be estimated at day 0 and day 28, using a hemocue for the quantitative determination of haemoglobin in blood using a specially designed photometer and micro-cuvettes.

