### Trial Data Analysis

Individual patient level pooled analysis of the data from the four sites will be conducted, according to CONSORT standards for reporting RCTs. A random effects model will be used to adjust for site and other covariates. To analyse for effect differences for the primary outcomes, intention to treat (ITT) principles will be used and additional sensitivity and per protocol (PP) analyses will be conducted separately. ITT implies that all randomised patients will be considered in the outcomes as per randomization. Missing data will be imputed as intervention failure (non-adherent or not report for post treatment review), using multiple imputation for missing data not directly related to adherence. The latter is considered the gold standard for handling missing data as it leads to unbiased estimates and standard errors compared to single imputation methods [31]. In the per protocol (PP) analysis, only patients completing the study and have been exposed to the intervention will be included. Category analyses will be conducted to investigate the relationship between adherence and treatment success (clinical and parasitological cure) at day 3. The study is powered adequately, so no interim analyses will be conducted.

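### A child whose AL was stopped because it got worse can be scored non-adherent, so the planned adherence-versus-cure analysis is open to reverse causation in category 3

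*Protocol article*

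**What the plan says.** The Primary outcomes section sets the first primary outcome as "adherence to a complete AL course (doses 2-6) measured in category 3 only". It has four levels. The lowest, level (d), is "non adherent if they present blister packs with at least one tablet not used". Where no pack is shown, the child is classed on the caregiver's report, and level (c) is "probably non adherent if they do not present blister packs and do not report taking the medications as recommended". None of the levels asks why a dose was not given.

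Three other statements bear on this:

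- Phase 2 – The randomized controlled trial: the first dose is observed and five are given at home. All caregivers are told "when to return to the facility for scheduled visits or immediately if unwell".
- Trial Data Analysis, on missing outcomes: "Missing data will be imputed as intervention failure (non-adherent or not report for post treatment review".
- Trial Data Analysis, on the secondary question: "Category analyses will be conducted to investigate the relationship between adherence and treatment success (clinical and parasitological cure) at day 3".

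Laboratory procedures provides a smear at the day 3 visit, at home or at the facility, and at every unscheduled visit. Cure status is therefore available for category 3.

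**The concern.** The instruction to return if unwell can bring a worsening child to a clinician before dose 6. If AL is then stopped or replaced, three routes can end in a non-adherent label:

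- The pack is shown with tablets left: level (d).
- No pack is shown: the level depends on how the caregiver's report is read, and (c) is possible.
- The child is admitted and the home visit yields no data: the missing-data rule scores it non-adherent. This route reaches the adherence-cure analysis only if the child's cure status is known from elsewhere, such as an unscheduled visit.

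In each case the caregiver may have followed every instruction. For adherence against cure, time order is lost because the failure comes first and the label follows. Randomisation gives no protection, because adherent and non-adherent children are not randomised groups. The bias always makes non-adherence appear to predict failure. The article's Background already names poor adherence as a driver of reduced cure and resistance, so a false result in that direction would be readily believed.

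The problem is strongest in category 3, the only group with full-course adherence. In categories 1 and 2 adherence is recorded on day 1 or 2, ahead of the day 3 assessment.

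**Working it through.** **1. The plan's own figure.** Sample size estimation gives 400 per arm in category 3, for 65% against 75%, 80% power, alpha 0.05 and 15% loss. Two-sided, pooled variance:

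n = [1.960·√(2·0.70·0.30) + 0.842·√(0.65·0.35 + 0.75·0.25)]² / 0.10² = 329 per arm; 329/0.85 = 388.

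This is within 3% of 400, so the figure reproduces. With 400 × 0.85 = 340 evaluable per arm, power is 81.3%.

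**2. Randomised comparison.** Let f be the share per arm with AL stopped early and scored non-adherent (assumed, equal in both arms). Take 65% and 75% as the rates without such stops. Both rates are multiplied by (1 − f):

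| f | Control | SMS | Difference (points) | Power, 340 per arm |
|---|---|---|---|---|
| 0 | 65.0% | 75.0% | 10.0 | 81.3% |
| 1% | 64.4% | 74.3% | 9.9 | 80.1% |
| 2% | 63.7% | 73.5% | 9.8 | 78.7% |
| 3% | 63.1% | 72.8% | 9.7 | 77.4% |

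If f differed by arm with no SMS effect, the false difference would be 0.65 × (0.02 − 0.01) = 0.65 points for 2% against 1%.

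**3. Adherence against cure, with no true link.** Let a be true adherence, g the day 3 failure rate (the same whatever the adherence) and s the share of failures with AL stopped early. All three are assumptions. Stopped failures are labelled non-adherent:

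- Failures labelled adherent: g(1 − s)a. Failures labelled non-adherent: g[1 − (1 − s)a].
- Cured, adherent: (1 − g)a. Cured, non-adherent: (1 − g)(1 − a).
- Odds ratio = [1 − (1 − s)a] / [(1 − s)(1 − a)].

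The failure rate g cancels, so rare failure does not reduce the odds ratio. With a = 0.70:

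| s | Calculation | Spurious odds ratio |
|---|---|---|
| 5% | 0.335 / 0.285 | 1.18 |
| 10% | 0.370 / 0.270 | 1.37 |
| 25% | 0.475 / 0.225 | 2.11 |
| 50% | 0.650 / 0.150 | 4.33 |

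At s = 25%, a = 0.65 gives 1.95 and a = 0.75 gives 2.33.

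**4. In children.** Take 800 children, 560 truly adherent, and 3% failing (24: 16.8 adherent, 7.2 not). With s = 25%, 6 are stopped, of whom 4.2 change label. Failure is then 12.6/555.8 = 2.27% against 11.4/244.2 = 4.67%, a risk ratio of about 2.1 where the truth is 1.0.

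**5. Check of two remedies, same scenario.**

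- *Separate class.* Remaining failures are g(1 − s)a and g(1 − s)(1 − a), and the odds ratio returns to 1.0.
- *Scoring only doses due before the stop.* Early failures then have fewer doses to miss. If 70% adherence over five doses is equal and independent per dose, two doses give 0.70^(2/5) = 86.7%. With a quarter of failures scored on two doses, 0.75 × 0.70 + 0.25 × 0.867 = 74.2% of failures count as adherent, and the risk ratio at 3% failure is about 0.82. With half, it is about 0.65. This errs in the other direction.

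**The case against.** The strongest reply is that the triggering event is not in the article. No section describes stopping or replacing AL, no rate is given, and a full protocol or analysis plan may cover it. That stands as a limit on size. It does not remove the point, because the printed definition has no exception and would give the wrong label if applied as written.

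A reader might infer three stronger things that the documents do not support:

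- *That any unused tablet makes a child non-adherent.* Level (d) needs a presented pack; without one, the caregiver's report decides.
- *That the first primary outcome is compromised.* Counting a child who did not receive all doses as not completing the course is a legitimate as-randomised definition, and the article wants comparability with previous studies. Nor does the article show a route to a difference between arms. The instruction to return goes to all caregivers, and the SMS prompts about an unwell child come on days 7, 14 and 21, after the course has ended.
- *That the adherence-cure analysis is certain to be badly wrong.* Cure includes a day 3 smear, and the dose 6 reminder goes out at 8 pm on day 2. Parasitaemia first found on day 3 cannot have caused unused tablets. Severe malaria and danger signs are excluded at entry. Shares of 5-10% are therefore plausible. Even at 25%, the example of 800 children gives a risk ratio of 2.06 with an approximate 95% interval of 0.94 to 4.5.

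The analysis is also observational, is given one sentence, and does not name the adherence levels or categories used. That limits its weight, but a large spurious association could still be reported from it.

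**Conclusion.** The point holds for the adherence-cure analysis in category 3. As printed, the scoring lets treatment failure produce the non-adherent label, so the analysis is open to reverse causation. The spurious odds ratio runs from about 1.2 to 1.4 if 5-10% of day 3 failures had AL stopped early, and from 2.1 to 4.3 if 25-50% did. These figures assume 70% true adherence and no real link; the stopping shares are not in the documents, and the low end is plausible.

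For the randomised first primary outcome the effect is negligible: 0.1 to 0.3 points of a 10-point difference at 1-3% stopped, with both arms reading slightly low. At 3%, power would be 77.4% instead of 81.3%, but only if the planning assumption of "Assuming a malaria treatment adherence of 65% with the current standard of care alone" excludes such children, which the article does not say. Nothing here calls for redefining that outcome.

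**What to change.** Leave the primary outcome definition as it is, and make two changes:

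1. On the existing home-visit and unscheduled-visit forms, record the date of and reason for any unused tablets. If this is not collected at the visit, it may not be recoverable later.
2. In Trial Data Analysis, for the adherence-cure analysis only, place children whose AL was stopped or replaced by a clinician, or who were admitted, before the course ended in a separate class rather than with the non-adherent. Run the main analysis among children still on AL through the scheduled last dose, and report the separate class alongside. Give two sensitivity analyses: the scoring as printed, and scoring of only the doses due before the stop. Under the assumptions above, with no true link, these two err in opposite directions.

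The cost is one date-and-reason field on each of the two forms and a sentence or two in the analysis section. The downside is that a few failures leave the main adherence-cure comparison, which may attenuate a true association. The change concerns scoring and analysis only; no clinical rule on stopping or replacing treatment is proposed.
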